## Abstract

**Background::**

Zao Ren An Shen (ZRAS), a Chinese Herbal Medicine product, has been proposed as an alternative to recommended treatments for chronic insomnia. There is a lack of strong evidence supporting this proposition.

**Aims::**

To assess the efficacy and safety of ZRAS capsule for chronic insomnia compared to placebo.

**Methods::**

A parallel-group, double-blind, randomized-controlled trial will be performed in Western Sydney University, Australia. After a 1-week placebo run-in, adults with chronic insomnia (n = 90) will be randomized in a 1:1 ratio to receive either ZRAS capsule or placebo for 4 weeks. Insomnia severity (Insomnia Severity Scale score), sleep parameters (measured with the Consensus Sleep Diary and actigraphy), fatigue levels (Fatigue Severity Scale score), psychological status (Depression Anxiety Stress Scale score), quality of life (Assessment of Quality of Life score), and adverse events will be assessed at baseline, mid-treatment, post-treatment and at a 1-month follow-up.

**Expected outcomes::**

We hypothesize that ZRAS capsule will improve insomnia severity, sleep parameters, fatigue levels, psychological status, and quality of life better than placebo at mid-treatment, post-treatment, and follow-up. We also hypothesize that the number of adverse events provoked by ZRAS capsule will be similar to placebo at these time-points.

**Trial registration::**

Australia New-Zealand Clinical Trial Registry (Registration number ACTRN12619000140156).

## Introduction

1

Insomnia disorder is a chronic dissatisfaction with sleep quantity or quality resulting in significant distress or daytime impairment.^[1,2]^ With a prevalence rate of 7.9% to 15% in the general population,^[3–5]^ insomnia disorder is the most common sleep disorder. Long regarded as a symptom of other disorders, insomnia has been found to be a risk factor for the development of depression,^[6]^ anxiety disorders,^[7]^ chronic pain,^[8]^ hypertension,^[9]^ cardiovascular disease,^[10]^ leading to an impaired health-related quality of life,^[11]^ and a higher mortality risk.^[12]^ Because of insomnia-related absenteeism, decreased productivity, and health care expenses, insomnia is also a burden for the society, with a cost evaluated at $5010 per person per year in Canada.^[13]^

Pharmacotherapy and psychotherapy are the only treatments recommended by current guidelines.^[14–17]^ Despite being the most common medication for insomnia,^[18]^ Benzodiazepine Receptor Agonists (BzRAs) have been found to induce a large range of adverse effects,^[15,19]^ have been associated with rebound insomnia and withdrawal symptoms,^[20]^ and there are concerns about dependence.^[21,22]^ Unsurprisingly, insomniacs have a preference for nonpharmacological approaches.^[23,24]^ Cognitive Behavioral Therapy for Insomnia (CBT-I), a set of psychotherapeutic interventions used specifically to treat insomnia disorder, has been proposed as an alternative. The efficacy of CBT-I for insomnia disorder is well established^[20]^; however, the lack of trained practitioners prevents most of insomnia patients to benefits from this therapy.^[25]^

As recommended treatments suffer from the above drawbacks, many insomnia patients resort to over-the-counter medication, Complementary and Alternative Medicine (CAM) and self-help methods.^[26–28]^ Chinese Herbal Medicine (CHM) is one of the most common treatments for insomnia in Chinese populations ^[29,30]^ and its use is increasing in Western countries.^[31]^ Recent systematic reviews of randomized-controlled trials (RCTs) suggest that CHM is relatively safe and can effectively improve sleep quality and sleep parameters.^[32,33]^ However, the need of evidence for individual formulas was highlighted.^[32]^

Zao Ren An Shen (ZRAS) is a CHM formula composed of 3 herbs, that is, Suan Zao Ren (Ziziphi Spinosae Semen), Wu Wei Zi (Schisandrae Chinensis Fructus) and Dan shen (Salviae Miltiorrhizae Radix et Rhizoma), which have all sedative effects and low toxicity.^[34–41]^ This formula, manufactured in the forms of capsule, granule and solution, is indicated for insomnia.^[42]^ Clinical trials on ZRAS have showed a better effect than placebo and a similar or better effect than BzRAs.^[43–57]^ Adverse events were also less reported by participant taking ZRAS compared to BzRAs.^[43,44,47–51,53,54,56,57]^ However, none of these studies used appropriate methods of randomization and blinding. There is a need for high-quality RCTs.

The objective of this study is to assess the efficacy and the safety of Zao Ren An Shen capsule compared to placebo for chronic insomnia. As ZRAS is proposed as an alternative treatment and not a first-line treatment, we will use placebo as a comparator with a superiority framework. The primary outcomes are insomnia severity measured with the Insomnia Severity Index (ISI) for efficacy and the number of adverse events (AEs) for safety. The primary endpoint is post-treatment (week 4). We hypothesize that ZRAS capsule will show a better efficacy than and a similar safety to placebo. Secondary outcomes include objective and subjective sleep parameters, fatigue levels, psychological status, quality of life, adherence, and acceptability. The secondary endpoints are mid-treatment (week 2) and follow-up (week 8).

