##### Adverse events

2.6.1.2

The participants will be encouraged to report any AE at any time during the intervention or follow-up period. A description of the AE will be recorded along with the seriousness, severity, relationship with the investigational product and expectedness of the AE in the AE form. The number of adverse events will be used as the primary outcome for safety. Serious adverse events will be reported to the Western Sydney University Human Research Ethics Committee and the Therapeutics Goods Administration. All significant safety issues and suspected unexpected serious adverse reactions will be reported within 72 hours to the trial site (Western Sydney University).

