### Statistical analysis

2.9

Continuous data will be analyzed with linear mixed effects model, the data being corrected for baseline characteristics; mean, standard deviation, effect size, 95% CI and *P*-value will be reported. Dichotomous data will be analyzed with Chi-square and counts, percentages, and *P*-value will be reported. We will analyze the final vale of the outcomes with a significance level of α=0.05. Both an intention-to-treat analysis and a per-protocol analysis will be conducted, the intention-to-treat analysis being of primary interest as it reflects better the effectiveness of the investigational product. The effect of expectancy and CM diagnosis on the trial outcomes will also be analyzed. The statistical analysis will be performed with SPSS 25 (IBM).

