## Discussion

3

The objective of this study is to assess if ZRAS is relatively safe and effective for chronic insomnia compared to placebo. This study, which has a stringent design with randomization and double blinding, will provide high-quality evidence for or against the use of ZRAS capsule as an alternative treatment for chronic insomnia.

If the hypothesis is verified (i.e., ZRAS is relatively safe and more effective than placebo), ZRAS may be recommended if the current recommended treatments (i.e., pharmacotherapy and CBT-I) are ineffective, not available or if the patient refuses these treatments. More RCTs comparing ZRAS capsule to pharmacotherapy or CBT-I would be also needed to assess if ZRAS should be used as a first line or alternative treatment. RCTs comparing ZRAS capsule in addition to recommended treatments to recommended treatments alone would help us to understand the value of adding ZRAS capsule to these treatments.

The strengths of this study are:

The use of a third-party randomization scheme with allocation concealment and double blinding.The use of a placebo similar in appearance and taste to the active.The combination of subjective (i.e., with the CSD) and objective (i.e., with actigraphy) measures of sleep.A comprehensive assessment encompassing fatigue, psychological status, quality of life, satisfaction and acceptability.The use of a CM diagnosis.

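### The primary safety hypothesis is similarity to placebo, but the plan names only a superiority framework and difference tests, so no planned analysis can verify it

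*Protocol article*

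**What the plan says.** All references are to the protocol article.

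- **Hypothesis.** Introduction (section 1): "We hypothesize that ZRAS capsule will show a better efficacy than and a similar safety to placebo". The abstract (Expected outcomes) repeats it for counts: "the number of adverse events provoked by ZRAS capsule will be similar to placebo at these time-points".
- **Outcome.** Adverse events (2.6.1.2): "The number of adverse events will be used as the primary outcome for safety". The Introduction lists it as primary beside the ISI.
- **Framework.** Introduction: "we will use placebo as a comparator with a superiority framework". No equivalence or non-inferiority framework appears anywhere.
- **Analysis.** Statistical analysis (2.9): "Continuous data will be analyzed with linear mixed effects model", for which an effect size and 95% CI are promised. For the other type of data: "Dichotomous data will be analyzed with Chi-square and counts, percentages, and *P*-value will be reported". The significance level is 0.05. The section does not say which of the two methods applies to an AE count.
- **Sample size.** Section 2.10 uses only ISI quantities: SD 4.1, a 7-point change against about 4 points on placebo, 90% power and 10% dropout.
- **Use of the result.** Discussion (section 3): "If the hypothesis is verified (i.e., ZRAS is relatively safe and more effective than placebo), ZRAS may be recommended", followed by the circumstances in which the recommendation would apply.

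**The concern.** A hypothesis of similarity is supported by showing that any excess of harm is smaller than some stated amount. A superiority framework with difference tests does the opposite. It can show that the arms differ, but failing to show this is not evidence that they are alike. With no margin and no interval rule, the plan gives no criterion by which the safety hypothesis could be called verified, although the Discussion relies on its being verified.

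If the gap is filled by the only criterion on offer, significance at 0.05, the incentive runs the wrong way: fewer participants, fewer events or noisier recording all make non-significance easier to reach. A report could then describe AEs as similar when the data are compatible with a substantial excess on ZRAS.

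**Working it through.** **1. The plan's own figure, and what enters it.** The difference is 7 − 4 = 3 ISI points, and 3/4.1 = 0.73 SD. With two-sided alpha 0.05 and 90% power, n per arm = 2(1.96 + 1.2816)²/(3/4.1)² = 21.0/0.535 = 39.3, so 40. Allowing 10% dropout, 40/0.9 = 44.4, so 45 per arm and 90 in total. The stated size is reproduced, and no safety quantity enters it.

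**2. Inputs for the safety check.** Arm size is 45 as planned, or 40 after the allowed dropout. The documents give no AE rate, so every rate below is an assumption shown as a range. The named outcome is a count, but chi-square would apply if AEs were dichotomised, so both forms are shown.

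**3. Participants with at least one AE.** Power of the uncorrected two-sided chi-square test at 0.05 is the sum of the two binomial probabilities over all outcome pairs with chi-square above 3.84.

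| True incidence, placebo to ZRAS | Power, 45 per arm | Power, 40 per arm |
|---|---|---|
| 10% to 20% | 0.277 | 0.247 |
| 15% to 30% | 0.416 | 0.366 |
| 20% to 40% | 0.563 | 0.497 |

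A normal approximation gives 0.26 and 0.55 for the first and third rows at 45 per arm, which agrees closely. By the same approximation, 80% power at 45 per arm needs a rise from 10% to about 34%, or from 20% to about 48%.

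Precision: the 95% half-width for the risk difference, 1.96√(2p(1−p)/45), is 12.4, 16.5, 18.9 and 20.2 percentage points at p = 0.1, 0.2, 0.3 and 0.4.

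Illustration: 17/45 against 9/45 gives P = 0.063. The difference is 0.378 − 0.200 = 0.178 with standard error √(0.378×0.622/45 + 0.2×0.8/45) = 0.094, so the 95% CI runs from about −1 to +36 points. The result is non-significant, yet an excess of more than 30 points is not excluded.

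**4. AE counts (the named outcome).** Assume Poisson counts with rate r per placebo participant and a true rate ratio RR. The standard error of log RR is √(1/(45r) + 1/(45r·RR)), and power is Φ(log RR/SE − 1.96). For r = 0.2 and RR = 2, SE = √(1/9 + 1/18) = 0.408, 0.693/0.408 = 1.70, and Φ(−0.26) = 0.40.

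| AEs per placebo participant | Power, RR = 2 | Power, RR = 1.5 | Upper 95% limit if observed RR = 1 |
|---|---|---|---|
| 0.2 | 40% | 15% | 2.52 |
| 0.5 | 77% | 32% | 1.79 |
| 1.0 | 97% | 56% | 1.51 |

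The last column is exp(1.96√(2/(45r))). Even with identical observed rates, the interval would reach ratios between about 1.5 and 2.5.

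**5. Could a margin be set at this size?** For non-inferiority on the proportion with an AE, with equal true rates p, one-sided 0.025 and 80% power, n per arm = (1.96 + 0.8416)²·2p(1−p)/m², before dropout. Margins are assumed.

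| AE rate | m = 10 points | m = 15 points | m = 20 points |
|---|---|---|---|
| 5% | 75 | 34 | 19 |
| 10% | 142 | 63 | 36 |
| 20% | 252 | 112 | 63 |
| 30% | 330 | 147 | 83 |

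With 40 to 45 evaluable per arm, the claim is feasible only at an AE rate near 5% with a 15-point margin, or up to about 10% with a 20-point margin.

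**The case against.** The strongest reply has five parts.

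- **No stated misreading.** A reader might infer that the protocol will take P > 0.05 as proof of safety. It never says so, and that reading should not be attributed to it. What stands is that the Discussion speaks of the hypothesis being verified and no other criterion is offered.
- **The recommendation is hedged.** A reader might also infer that the trial would declare ZRAS as safe as placebo and recommend it outright. The Discussion says only relatively safe, limits the recommendation to cases where standard treatments fail, are unavailable or are refused, and calls for further trials. This softens the consequence but supplies no test of similarity.
- **The outcome is a count.** Chi-square miss rates are therefore not a property of this protocol. If AEs are frequent, power to detect a doubling is high. This is correct, and is why the count results are given. They do not repair the logic, and power for a ratio of 1.5 stays low or moderate.
- **An interval may already be planned.** If AE counts go into the mixed model, section 2.9 promises a 95% CI, so it would be wrong to say that no interval will exist. There is still no stated excess against which to judge it.
- **Framework and delegation.** The superiority phrase sits in a sentence explaining the choice of placebo and may be meant for efficacy only. The AE model and interpretation rule are often left to the analysis plan, and sizing on the efficacy outcome is ordinary. All fair. But the similarity hypothesis on a primary outcome, and the statement conditioned on it, are fixed in this document, with no framework suited to them.

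**Conclusion.** The concern holds in this form: the protocol states a similarity hypothesis for a primary outcome and conditions a recommendation on it, yet names no framework, margin or analysis capable of verifying it. This follows from the text and needs no assumption about AE rates.

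The practical size does depend on assumed rates. At 45 per arm a true doubling would go undetected in about 44% to 72% of trials if 10% to 20% of placebo participants have an AE. For Poisson counts at 1.0, 0.5 or 0.2 events per placebo participant the figure is about 3%, 23% or 60%. The problem is serious if AEs are uncommon and mild for a doubling if they are frequent. The efficacy hypothesis, its sample size and the ISI analysis are unaffected.

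**What to change.** Before the allocation codes are broken:

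1. Replace the similar-safety hypothesis in the Introduction and in the abstract's Expected outcomes with an estimation objective.
2. In section 2.9, specify the ZRAS/placebo AE rate ratio from a count model, since the count is the named outcome, and the risk difference in participants with at least one AE, each with a 95% CI.
3. State that a non-significant difference will not be interpreted as similarity.
4. Reword the Discussion sentence so that its safety statement rests on those intervals.

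The cost is wording and two intervals, with no extra participants. The real price is that the trial gives up a claim of similar safety. Adding a non-inferiority margin is not the recommended route: 40 to 45 evaluable per arm would support it only if AEs are rare or the margin is wide.

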## Methods

2

### Study design

2.1

This study will use a randomized, double-blind, placebo-controlled design with a 1:1 allocation ratio and parallel groups. After 1 week of single-blinded placebo run-in, the participants will be randomized to the experimental group or the control group and take Zao Ren An Shen (ZRAS) capsule or a placebo, for 4 weeks. Outcomes will be assessed at pretreatment, mid-treatment, post-treatment, and at a 1-month follow-up (Tables 1 and 2).

**Table 1 T1:**
[figure not shown]
Trial procedures.

**Table 2 T2:**
[figure not shown]
Trial registration data.

### Settings

2.2

The 3 visits of the trial will be conducted at 4 campuses of Western Sydney University, that is, Parramatta City campus, Bankstown Campus, Westmead campus, and Campbelltown campus around Sydney, Australia.

### Participants

2.3

#### Recruitment strategy

2.3.1

Participants will be recruited through advertisement and referrals from the February 15, 2019 to the November 29, 2019. Ads will be put in social media (e.g., Facebook and Wechat) and poster and flyers in public places (e.g., Universities, libraries), pharmacies and healthcare practices. Pharmacists and general practitioners around the trial sites will be contacted for potential referrals.

#### Eligibility criteria

2.3.3

The eligibility criteria, based on the diagnosis criteria for insomnia disorder (307.42) from the DSM-5,^[1]^ are as following:

Inclusion criteria:

1.18 years old or older.2.Complaint of difficulty initiating or maintaining sleep occurring at least 3 times per week for at least 3 months despite adequate opportunity to sleep, and resulting in distress or impaired daytime functioning.3.ISI score ≥ 10.4.Willing to abstain from any other treatment for insomnia, including pharmaceutical treatment, CAM, and psychotherapy, during the baseline and intervention periods.5.Willing to use birth control methods and to not donate sperm during the baseline and intervention periods, or sterile.6.Ability to understand and speak English.

Exclusion criteria:

1.Imminent need of psychiatric (e.g., suicide risk) or medical care (e.g., stroke).2.Abnormal blood tests, including FBC, LFT, and electrolytes-urea-creatinine, within the last 6 months, if not approved by a general practitioner.3.No evidence that substance use (e.g., caffeine or a medication), coexisting medical conditions or mental disorders, including sleep–wake disorder, do not adequately explain the predominant complaint of insomnia.4.Use of any other treatment for insomnia less than 14 days prior to randomization.5.Any psychotic disorder or bipolar disorder if not appropriately treated or stable for <2 years.6.Alcohol or drug addiction.7.Other mental disorders such as major depressive disorder or generalized anxiety disorder, if the disorder is untreated or treated for less than one month.8.Cognitive impairment preventing the participant to understand the trial instructions, complete questionnaires or provide informed consent.9.Allergy history to any of the ingredient of the ZRAS capsule or the placebo.10.Taking a Warfarin-type anticoagulant,^[58,59]^ quetiapine, clozapine, or olanzapine.^[60]^11.Women being pregnant or breast feeding.12.Considered not suitable for the trial by the investigator.

### Randomization and blinding

2.4

A randomization sequence without stratification will be generated using computer-generated random numbers by a NICM Heath Research institute researcher not directly affiliated with this study to ensure blinding. The sequence generated will be used to identify the investigational product. The participants will be randomized during the second visit of the trial. Both the investigator and the participants will be blinded at recruitment and during the intervention. The codes will be broken in case of emergency, such as a serious adverse event that requires knowledge of the treatment being taken in order to manage a participant's condition.

### Interventions

2.5

The investigational product is ZRAS capsule, a CHM product composed of Suan zao ren (Ziziphi Spinosae Semen, 417 mg/capsule), Wu Wei Zi (Schisandrae Chinensis Fructus, 70 mg/capsule), and Dan Shen (Salviae Miltiorrhizae Radix et Rhizoma, 167 mg/capsule). The placebo, composed of microcrystalline cellulose, calcium hydrogen phosphate dehydrate, carob pod powder, silicon dioxide, and magnesium stearate, matches the active in terms of appearance and taste. The participant will be asked to take 3 capsules of placebo (2.16 g in total) orally once a day one hour before bedtime for one week. After randomization, the participant will be asked to take 3 capsules of ZRAS (2.28 g in total) or placebo (2.16 g in total) orally once a day one hour before bedtime for 4 weeks. Both ZRAS capsule and the placebo were provided by Global Therapeutics, Pty, Ltd. The participant will be asked to refrain from taking any other treatment for insomnia during the week preceding and the 5 weeks following the first visit, except for rescue medication.

### Assessments

2.6

#### Primary outcomes

2.6.1

##### Insomnia severity

2.6.1.1

Insomnia severity will be measured with the Insomnia Severity Index (ISI). The ISI ^[61]^ is a brief 7-item scale used to assess perceived insomnia severity and consequences in accordance with the diagnostic criteria for insomnia of the Diagnostic and Statistical manual of Mental Disorders, 4th edition, and the International Classification of Sleep Disorders. Unlike the Pittsburgh Sleep Quality Index, another questionnaire commonly used for insomnia assessment, the ISI is specific to insomnia disorder. The ISI has good psychometric properties ^[61]^ and can be used to detect insomnia cases and evaluate treatment response.^[62]^ The range of the scale is 0 to 28 points and the score is positively associated with insomnia severity.

##### Adverse events

2.6.1.2

The participants will be encouraged to report any AE at any time during the intervention or follow-up period. A description of the AE will be recorded along with the seriousness, severity, relationship with the investigational product and expectedness of the AE in the AE form. The number of adverse events will be used as the primary outcome for safety. Serious adverse events will be reported to the Western Sydney University Human Research Ethics Committee and the Therapeutics Goods Administration. All significant safety issues and suspected unexpected serious adverse reactions will be reported within 72 hours to the trial site (Western Sydney University).

#### Secondary outcomes

2.6.2

##### Questionnaires

2.6.2.1

The Depression Anxiety Stress Scale 21-item ^[63]^ is a self-report questionnaire composed of 21 items assessing the levels of depression, anxiety, and stress of the subject. The Assessment of Quality of Life ^[64]^ questionnaire is a self-report instrument used to assess health-related quality of life. This study will use the 4-dimension version of the questionnaire, which measures independence, relationships, mental status, and senses. The Fatigue Severity Scale ^[65]^ is a 7-point Likert scale that measures different aspects of fatigue. The questionnaires used in this study have all acceptable psychometric properties.^[64,66,67]^

